### Theoretical Framework and Logic Model

The FT4W program is founded on social cognitive theory, which posits that human behavior is the product of the dynamic interplay of personal, behavioral, and environmental influences [17]. Social cognitive theory emphasizes reciprocal determinism in interactions between people and their environments. The majority of physical activity interventions use social cognitive theory as indicated by the theory and technique tool developed by the Human Behaviour Change Project [18]. We used the theory and technique tool to align the FT4W program components and mediating pathways with behavior change techniques and mechanisms of action substantiated in behavior change literature and expert consensus. Studies that use behavior change techniques of restructuring the physical environment and peer support show that the mechanisms of action are environmental context and resources (aspects of a person’s situation or environment that discourage or encourage the behavior) and social influences (interpersonal processes that can cause oneself to change one’s thoughts, feelings, or behaviors) [18]. For our study, we will measure social influence via social cohesion.

Our logic model (Figure 1) illustrates the 2 complementary components of the FT4W program and mediating pathways in which the intervention can be effective. We hypothesize that providing free childcare during free fitness classes can provide environmental resources that participants can use to increase their physical activity. We hypothesize that this effect will be stronger in participants who also receive peer support, the intervention component that creates social cohesion. We also hypothesize that the effect of the intervention will differ based on race and ethnicity and other social stratifiers (migration status, SEP, and gender or sexual orientation).

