#### Analyses

##### Quantitative Analysis

The primary analyses will be on the intention-to-treat sample: all randomized participants according to the assigned treatment. Missing data on outcome variables will be dealt with by using multiple imputation or inverse probability weighting of cases with complete data, where we will calculate weights based on the probability of a participant being a completer versus a dropout. We will conduct a sensitivity analysis to provide a range of plausible effect estimates that could arise due to nonignorable missing data.

For aims 1 and 2, we will use linear mixed-effects models (LMMs) to assess the main intervention effects on physical activity outcomes and other secondary outcomes. The outcome measure of interest will be the dependent variable; the treatment arm (categorical variable with 3 categories) will be the predictor. Cluster-specific random intercept will account for intraclass correlation. We will further adjust the model for baseline covariates that are not balanced across treatment groups (if any). Comparison of treatment arms can be tested by forming contrasts of regression coefficients in the models.

We will conduct mediation analysis to test whether environmental resources and social cohesion, described under working mechanisms, mediate the intervention effects. For each mediation analysis, we will conduct 2 LMM analyses. The first model will use the outcome measure as a dependent variable and treatment arm and mediator as predictors. The second model will use the mediator as a dependent variable and treatment arm as the predictor. Both models will include a cluster-specific random intercept to account for intraclass correlation. Causal mediation effects will be tested using the R package *mediation*. For aim 3, moderator analysis will examine whether intervention effects differ across social stratification parameters (stratifier) at the individual and community levels. We will conduct a similar LMM analysis as in the main effect analysis, with the exception that each stratifier and its interaction with the treatment arm will be included in the LMM. The moderator effect will be examined by testing the stratifier by treatment interaction effect coefficients.

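### The mediation outcome model assumes one mediator slope for all three arms, with no stated check, so its causal indirect effects are averages over arms if the slopes differ

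*Protocol article*

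**What the plan says.** The Quantitative Analysis section gives the purpose of the analysis: "We will conduct mediation analysis to test whether environmental resources and social cohesion, described under working mechanisms, mediate the intervention effects". Two linear mixed models are then defined. For the outcome, "The first model will use the outcome measure as a dependent variable and treatment arm and mediator as predictors". For the mediator, "The second model will use the mediator as a dependent variable and treatment arm as the predictor". On the random part, "Both models will include a cluster-specific random intercept to account for intraclass correlation". The results carry a causal label: "Causal mediation effects will be tested using the R package" named mediation.

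The moderator analysis, in the same paragraph, does name an interaction: it follows the main-effect model "with the exception that each stratifier and its interaction with the treatment arm will be included in the LMM".

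The Theoretical Framework and Logic Model section gives the expected mechanism in two steps. First, "We hypothesize that providing free childcare during free fitness classes can provide environmental resources that participants can use to increase their physical activity". Then, "We hypothesize that this effect will be stronger in participants who also receive peer support, the intervention component that creates social cohesion".

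**The concern.** A model with arm and mediator as main effects gives the mediator the same slope in every arm. The logic model says that the childcare effect, which is expected to run through resources, is stronger when peer support is added. One natural reading is that the same resources produce more activity in arm C than in arm B. On that reading the slope differs between arms, and the model as written cannot show it.

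At stake is the explanation of the trial's result. If the slope is steeper in arm C, a pooled slope understates how much of the arm C effect runs through the mediator at that arm's conditions, and the direct effect absorbs the difference. The B versus A indirect effect can be overstated at the same time. The article uses the mediation results, together with the ethnography, to explain why the programme does or does not work.

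**Working it through.** The article gives no numerical input or result for the mediation analysis, so there is no figure to reproduce. Mediator shifts and slopes below are assumptions, in SD units. From Sample Size come 7 sites per arm, 15 analysable participants per site and an intraclass correlation of 0.15.

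**Step 1: what the common slope estimates.** With equal arm sizes and equal mediator variance within arms, it is the mean of the arm slopes:

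pooled slope = (b_A + b_B + b_C) / 3.

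The reported indirect effect is (difference between arms in the mediator) × (pooled slope). With an interaction, the same mediator difference is multiplied by the slope of one arm of the contrast, which gives one value per arm.

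**Step 2: only arm C shifts the mediator, by 0.5.**

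| Slopes A / B / C | Pooled slope | C vs A as written | At A slope | At C slope |
|---|---|---|---|---|
| 0 / 0.15 / 0.30 | 0.45/3 = 0.15 | 0.5 × 0.15 = 0.075 | 0 | 0.15 |
| 0 / 0 / 0.30 | 0.30/3 = 0.10 | 0.5 × 0.10 = 0.05 | 0 | 0.15 |
| 0.30 / 0.30 / 0.30 | 0.30 | 0.5 × 0.30 = 0.15 | 0.15 | 0.15 |

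Simulation at trial size agrees: 0.074 to 0.076 in the first row and 0.050 in the second. In the first row the C versus B shift is also 0.5, so the model gives 0.075. That is the correct value at arm B's slope (0.5 × 0.15) and half the value at arm C's slope (0.15).

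**Step 3: both B and C shift the mediator, by 0.5 and 0.8.**

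- Slopes 0.2 / 0.2 / 0.4: pooled 0.8/3 = 0.267. B vs A is 0.5 × 0.267 = 0.133, against 0.5 × 0.2 = 0.100, which is 33% too high. C vs A is 0.8 × 0.267 = 0.213, against 0.160 (A slope) and 0.320 (C slope). One large simulated sample, whose fitted arm slopes were 0.206, 0.213 and 0.420, gave a pooled slope of 0.280, a B vs A value of 0.140 (40% too high) and a C vs A value of 0.224. The gap from 33% is sampling error in that sample.
- Slopes 0.1 / 0.3 / 0.5: pooled 0.3. B vs A is 0.150, against 0.050 (A slope) and 0.150 (B slope). C vs A is 0.240, against 0.080 and 0.400.

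**Step 4: precision.** A slope from one arm uses a third of the data, so its standard error is about √3 = 1.7 times that of the common slope. Simulation gave 0.056 (common) and 0.097 (arm-specific), a ratio of 1.7. For a true common slope of 0.15, two-sided 5% power is about Φ(0.15/0.056 − 1.96) = Φ(0.72) = 76% with the common slope and Φ(0.15/0.097 − 1.96) = Φ(−0.41) = 34% with one arm's slope.

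**Step 5: can the trial detect unequal slopes?** With 7 × 15 per arm, the two-degree-of-freedom interaction test had about 30% power for slopes 0.2 / 0.2 / 0.4 and about 70% for 0.1 / 0.3 / 0.5. These are approximate: 200 replicates, some with convergence warnings.

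**The case against.** The strongest reply is that the hypothesis is a statement about arms. It says that participants who receive peer support benefit more, and the C versus B contrast in the main model tests that. A larger effect in arm C also arises with equal slopes, if peer support raises cohesion and cohesion acts alike everywhere. With no arm that has peer support but no childcare, the trial cannot separate synergy from an added effect. This stands. A reader might infer that the plan contradicts its own hypothesis, or excludes the mechanism it sets out to test. The documents do not support that, because no passage says that the slope of activity on resources or cohesion differs by arm.

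A reader might also infer that the indirect effects are wrong for every arm. They are not: with equal slopes there is no bias, and with slopes 0 / 0.15 / 0.30 the pooled slope is arm B's own slope.

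The precision argument also stands. If the slopes are equal, relying on arm-specific slopes alone gives up much power, so the additive model is a defensible choice with 21 classes and should stay.

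Finally, a condensed article may leave model options to the analysis plan. This stands only in part. The article lists the terms of the outcome model and names an interaction in the neighbouring moderator analysis, so the fair reading of the mediation model is main effects only.

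**Conclusion.** The point holds in a limited form. As written, the mediation outcome model assumes equal mediator slopes in the three arms, states no check of that assumption, and labels the result causal. If the slopes differ, which the complementary-components theory allows, the indirect effect is an average. In the assumed cases it was half or a third of the value at the arm C slope (0.075 or 0.05 against 0.15), and elsewhere a third too high for B versus A. These sizes depend entirely on assumed slopes and mediator shifts, for which the article gives no values. A slope of zero in arm A in particular has no basis in the documents.

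This is a secondary mechanism analysis, and the arm contrasts for aims 1 and 2 do not depend on it. The change is worth making before the data are analysed, but the trial's main conclusion does not hang on it.

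**What to change.** In the mediation paragraph of Quantitative Analysis, or in the analysis plan if it governs, prespecify a second outcome model that adds the arm-by-mediator interaction. For B versus A and for C versus B, report the indirect and direct effects at the slope of each arm in the contrast, with confidence intervals, beside the common-slope results. Report the interaction test. Label the common slope as an assumption. State that a non-significant interaction will not be read as evidence of equal slopes, since its power is only about 30% when arm C's slope is double the others.

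The cost is one more model per mediator and a few more table rows. The arm-specific estimates will be less precise, with slope standard errors about 1.7 times larger, which is why they belong next to the common-slope results and not in their place.

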#### Sample Size

We powered the study to compare the main intervention effects on the primary outcome, which is the average time spent in moderate to vigorous physical activity (MVPA) per week. We plan to enroll 7 sites per study arm (excluding the pilot wave), with about 30 participants with up to 45 children per site. We assume an attrition rate of 30% based on our feasibility study as well as another similar study [19] and an additional 25% accelerometer nonadherence rate based on previous studies [19,20], yielding an average 15 participants per site. Previous studies show that the intraclass correlation coefficient is ~0.15, and we expect a coefficient of variation of 0.5 in the number of participants across different sites. For aim 1, with 80% power, the minimum detectable effect size for the comparison of intervention arm B versus control arm A on average time spent in MVPA is Cohen *d*=0.68 at 5% significance. For aim 2, we will use the Bonferroni correction to adjust for multiple comparisons of arm C versus arm B and arm C versus arm A. With 80% power, the minimum detectable effect size for each comparison is Cohen *d*=0.75 at 5% significance. A previous physical activity intervention study with mothers led to an 80-minute increase in average time spent in MVPA [20]. Specifically, at posttest, the experimental group performed a mean of 154.8 (SD 45.3) minutes of physical activity, whereas the control group reported a mean of 74.6 (SD 44.4) minutes. This yields an effect size of *d*=1.8; thus, we are adequately powered for aims 1 and 2. Finally, quantitative analyses are not fully appropriate to examine intersectionality (eg, too reductionist), rendering a power analysis inappropriate; instead, we will integrate the statistical analysis with qualitative data to evaluate aim 3.

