While 21 clusters are on par with the average cluster size in cluster RCTs, we still need to correct for the small sample since type I error can be up to ~7% for studies with 20-40 clusters [45]. For our continuous outcomes, residual (restricted) maximum likelihood will be used [46]. We will also adjust the test statistic to a 2-tailed *t* test with 2K–2 degrees of freedom if cluster structures are balanced [47]. If cluster sizes vary, alternative small sample corrections will be used. As a sensitivity analysis, cluster-level analysis will also be conducted. We will perform a 2-tailed *t* test on the cluster-level means of physical activity.

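### The stated detectable effects (d=0.68 and d=0.75) assume normal quantiles and equal cluster sizes, although the plan requires a small-sample t correction and expects cluster sizes to vary

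*Protocol article*

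**What the plan says.** **Sample Size.** The design has 7 sites per arm without the pilot wave, an average of 15 analysable participants per site, and an intraclass correlation of about 0.15. On cluster size the section says "we expect a coefficient of variation of 0.5 in the number of participants across different sites". The aim 1 result, for arm B against arm A at 80% power, is stated as "on average time spent in MVPA is Cohen *d*=0.68 at 5% significance". The multiplicity rule of the second aim reads: "we will use the Bonferroni correction to adjust for multiple comparisons of arm C versus arm B and arm C versus arm A". The figure there is d=0.75 for either contrast, at the same power. The section concludes that power is adequate because an earlier intervention study in mothers gives d=1.8.

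**Quantitative Analysis.** The primary analysis is one linear mixed model with a three-category arm variable and a random intercept for cluster. Arms are compared by contrasts. The section notes that type I error can reach about 7% with 20-40 clusters and commits to restricted maximum likelihood. It then moves the test to a two-tailed t reference by a 2K–2 rule, which carries a condition: "degrees of freedom if cluster structures are balanced". When that condition fails, the section offers only this: "If cluster sizes vary, alternative small sample corrections will be used". A t test on cluster means is planned as a sensitivity analysis.

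**The concern.** The two sections do not describe the same test. The analysis section replaces the normal reference with a t distribution because clusters are few. The sample size section expects unequal clusters. If the detectable effects use neither feature, they are too favourable and the 80% power attached to them is wrong.

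The degrees-of-freedom rule is a second, smaller problem. It depends on balance, which the plan's own coefficient of variation contradicts. It is also a two-arm formula attached to a three-arm model, and K is not defined. At stake are the accuracy of the stated power for both aims and the clarity of the reference distribution for the primary test.

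**Working it through.** **Inputs (Sample Size section).** K=7 clusters per arm; m=15 analysable per cluster (30 × 0.70 × 0.75 = 15.75, given as 15); ICC=0.15; CV=0.5; power 80%; two-sided alpha 0.05 for aim 1 and 0.05/2 = 0.025 per comparison for aim 2.

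**Step 1: reproduce the stated figures.**
- Design effect for equal sizes: 1 + (15 − 1) × 0.15 = 3.10.
- Standard error in SD units: √(2 × 3.10 / (7 × 15)) = √(6.2/105) = 0.2430.
- Aim 1: (1.960 + 0.842) × 0.2430 = 0.681.
- Aim 2: (2.241 + 0.842) × 0.2430 = 0.749.

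These are the plan's 0.68 and 0.75. With K=7, values of m of 13.5, 15, 15.75 and 16 were tried with and without the CV, and with normal and t references. No combination using the CV or a t reference gave the pair.

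**Step 2: add CV 0.5.** The document does not say which approximation it would use, so two standard ones give a range.
- Relative-efficiency form: λ = 15/(15 + 0.85/0.15) = 0.726. Design effect = 3.10 / (1 − 0.25 × 0.726 × 0.274) = 3.26, standard error 0.2493.
- Inflated design effect: 1 + ((0.25 + 1) × 15 − 1) × 0.15 = 3.66, standard error 0.2641.

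**Step 3: degrees of freedom.**
- Three-arm model, 21 clusters, no wave terms: 21 − 3 = 18.
- 2K–2 with K=7: 12.
- Two-sided critical values at 5% / 2.5%: 2.10 / 2.45 (18 df) and 2.18 / 2.56 (12 df), against 1.96 / 2.24 for the normal.

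**Step 4: detectable effect.** This is the d at which 1 − F(t_crit; df, d/SE) = 0.80, where F is the noncentral t distribution function. Cells show aim 1 / aim 2.

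| Cluster sizes | Normal | t, 18 df | t, 12 df |
|---|---|---|---|
| Equal (3.10) | 0.68 / 0.75 | 0.72 / 0.81 | 0.74 / 0.84 |
| CV 0.5, relative efficiency (3.26) | 0.70 / 0.77 | 0.74 / 0.83 | 0.76 / 0.86 |
| CV 0.5, inflated design effect (3.66) | 0.74 / 0.81 | 0.78 / 0.88 | 0.81 / 0.91 |

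**Step 5: power at the stated d=0.68 / d=0.75.**

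| Cluster sizes | Normal | t, 18 df | t, 12 df |
|---|---|---|---|
| Equal | 80% / 80% | 75% / 73% | 73% / 70% |
| CV 0.5, relative efficiency | 78% / 78% | 73% / 71% | 71% / 67% |
| CV 0.5, inflated design effect | 73% / 73% | 68% / 65% | 66% / 62% |

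**Step 6: is 12 df safe in the three-arm model?** A simulation of the three-arm REML model (20,000 runs, nominal 5%) gave type I error for B versus A of 4.3% with 12 df, both balanced and at CV 0.5. With 18 df it gave 5.0% and 5.1%. The simulation assumes normal data, gamma-distributed cluster sizes (minimum 2) and no wave effects.

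**The case against.** The strongest reply is that the plan does protect the test. It commits to restricted maximum likelihood, a t reference and some small-sample correction when sizes vary. The exact correction is normally named in the SAP, which is not shown. This stands: the unnamed correction alone would not be a finding. A reader might infer that the primary test has no valid rule, but the text does not support that. With 7 sites per arm, K=7 is the natural reading, and 12 df errs on the safe side. It also equals the residual df if the seven waves were fitted as blocks (21 − 1 − 2 − 6 = 12), although the model described has no wave term.

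A reader might also take K as all 21 clusters, giving 40 df and a true error near 5.8% at a nominal 5%. Nothing in the section says so, and 2K–2 is the formula for K clusters per arm. Nor does the text show that the correction would be picked on the outcome result, since its stated trigger is variation in cluster size.

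On the figures themselves, one other combination among those tried also rounds to 0.68 and 0.75: 8 clusters per arm, 13.5 participants per cluster, the relative-efficiency correction and 46 df (0.678 / 0.751). It contradicts the stated 7 sites and average of 15, and 46 df exceeds what 24 clusters in three arms can supply (24 − 3 = 21). It does not rescue the stated values.

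Finally, the plan rests adequacy on d=1.8, and the largest restated value is 0.91. This also stands: the arithmetic gives no ground for calling the trial underpowered on the plan's own argument.

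**Conclusion.** The point holds as an error in the stated figures and a poorly fitted degrees-of-freedom rule. On the plan's own inputs, the detectable effects are about 0.74-0.81 for aim 1 and 0.83-0.91 for aim 2 across the two df values and two CV approximations. At the published effects, power falls short of 80% by roughly 7 to 14 percentage points for aim 1 and 9 to 18 for aim 2. The 2K–2 rule depends on a balance that the plan does not expect and is written for two arms. Read as 12 df, it costs some power but does not inflate error.

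These results assume ICC 0.15, 15 analysable participants in each of 7 clusters per arm on average, no gain from baseline adjustment, and independent clusters. The 18 df value also assumes no wave terms.

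**What to change.** 1. In Sample Size, restate both detectable effects with the t reference that the analysis will use and with CV 0.5. Name the CV approximation and the degrees of freedom.
2. In Quantitative Analysis, replace the balance-dependent 2K–2 rule with one small-sample correction that holds for unequal cluster sizes in the three-arm model, applied to all arm contrasts. Kenward-Roger, Satterthwaite or a fixed between-cluster df would each serve. If a formula in K is kept, define K.
3. Make sure that the chosen correction can be carried through the planned multiple imputation or weighting.

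The cost is a few sentences and slightly less favourable stated figures. The design, sample size and adequacy statement against d=1.8 need not change. Recruitment is still open, so the correction can be fixed before primary completion.

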##### Qualitative Analysis

We will thematically code the ethnographers’ field notes and transcribe participant interviews for both deductive and inductive codes. A codebook will be created using thematic coding by reviewing field notes and transcripts, grouping information into meaningful categories, and creating descriptive labels. The ethnographer will apply the codes to all text. The PI will double-code 10% of the content. We will develop themes from the codes and assess where themes converge and diverge across the ethnographic case-control sample.

##### Quantitative and Qualitative Data Integration

Mixed methods analysis will integrate the cluster RCT results with the ethnographic data to better understand the underlying processes explaining why the intervention is or is not effective (Figure 3). Quantitatively, we will assess effectiveness and mediation. We will also test for additive interaction by stratifying the average effect from statistical models by race and ethnicity and income. However, because intersectionality is not additive, we will heavily rely on qualitative data analysis to understand how intersecting forms of social inequality shape participants’ physical activity, environmental resources, and social cohesion, all components that influence effectiveness as indicated in our logic model (Figure 1).

